### Interventions

This research encompasses the evaluation of two investigation products that are supplied by KL-Kepong Oleomas Sdn Bhd. The first product, known as DavosLifeE3 Complete (50 mg), contains 50 mg of tocotrienols that are sourced from palm oil and meets the specifications outlined in the US Food and Drug Administration “generally recognized as safe” exemption claim 21 CFR 170.36 (c) [98]. The second product, Placebo Softgel, is a palm oil supplement that has the vitamin E compounds stripped off, serving as a vital control within the study. The blinding of the supplement is performed such that each group is labelled with their respective intervention product (IP) number without disclosing the content in the softgel. The softgels for both groups are odorless, of similar size and shape, and packaged in a fully opaque bottle. Contract research assistants generated the random allocation sequence, enroll participants, and assign participants to the interventions. Study participants, researchers, and data analysts will remain blinded throughout the clinical study to maintain blinding integrity throughout the 6-month intervention period.

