### Assignment of Interventions

Tocotrienols and placebo supplements are prepared and labelled with the IP number by the sponsor. Assignment of supplements to participants is by chance through the drawing of lots by contract research assistants. The treatment is double-blinded throughout the study period until all data have been collected and analyzed, after which the supplementation IP numbers are revealed to the PI by the sponsor. However, in case of any serious adverse event reported during the study period, the unmasking of the code is immediate.

A set of numbers, from 1 to 60, is randomized using the randomization application for every block of 60 participants. The participants are assigned a randomized number according to the numerical sequence 1 to 60 in the list of randomized numbers. All even numbers are treated with the same IP, while odd numbers are treated with another IP. Thus, every block randomization has an equal number of participants for each IP. The randomization will be repeated until 220 participants are recruited.

The unblinding in emergency situations is only permitted in case of a suspected, unexpected serious adverse reaction or other important adverse event, when knowledge of the supplemented product in question is required for therapeutic decisions in the medical management of the participant.

In the event of an emergency, an emergency decoding option is accessible to both the PI and designated personnel at the sponsor. The responsibility for breaking the blind for individual participants in emergency situations lies with the PI. If the need to break the blind arises, the PI will communicate this to the sponsor. Before the treatment code is broken, the PI responsible for unblinding must document the reason and date for unblinding in the case report form (CRF) to ensure proper documentation of the unblinding event, including a clear explanation of the reason for unblinding.

In the event that the sponsor requires unblinding of the treatment, the reason and date of unblinding are recorded in the CRF. In situations where it is necessary to unblind an individual participant’s treatment for the purpose of expedited reporting to the authorities, only designated individuals at the sponsor who are responsible for reporting this information will have access to the identity of the product. Every effort is made to ensure that all other members of the clinical trial remain blinded throughout the entire duration of the trial.

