### Analyses

Statistical analysis is conducted using SPSS (IBM Corp). The Kolmogorov-Smirnov test will be performed to assess the normality of the data distribution. Type III sum of squares is set to evaluate the hypotheses.

A mixed-design ANOVA will be used to determine whether supplementation affects the blood biochemistry parameters (inflammation and oxidative stress) and physical health (body composition, skin, cognitive function, and vascular health) at baseline, 3 months, and 6 months among the groups. The Mauchly test of sphericity will be conducted to assess homogeneity of variance and compare the means of the supplemented group with those of the placebo group. To account for the risk of a Type I error as a result of many primary and secondary outcomes, multiplicity correction procedures will be used. In particular, the Benjamini-Hochberg approach for false discovery rate control will be used in each outcome domain (eg, oxidative stress markers, inflammatory markers, cognitive tests). Statistical power and Type I error control are balanced for exploratory research in this method with connected variables. The Tukey post hoc test will be used for comparisons between groups, while the Dunnett test will be used for comparisons within groups over time. In terms of missing data, linear mixed-effects models with the missing at random assumption will be used, which is acceptable given the repeated-measures design and inclusion of observed predictors. Nevertheless, dropout rates in older adult groups might differ from missing at random (for example, because of undetected health decline). To evaluate the possible impact of data missing not at random, sensitivity analyses will be conducted using pattern-mixture models and multiple imputation with delta-adjustment scenarios. These methods aid with determining the robustness of the findings under alternate missingness assumptions. All data will be presented as mean (SD), with statistical significance defined as *P*<.05.

This study requires a total of 220 volunteers as calculated using the power and sample size program. In the case where any participant withdraws or is eliminated during the course of the project, their ID number is not reused. Instead, new volunteers are recruited to maintain the total sample size at 220. The distribution of the IP numbers is rerandomized and adjusted as needed to ensure that both groups remain equally balanced, with 110 participants receiving each IP.

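### Only two group-level product numbers serve all 220 participants, so one code break that reaches the principal investigator can reveal every arm; the unblinding triggers conflict, and one staff group generates the list, enrolls and assigns

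*Protocol article*

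**What the plan says.** **Product codes.** Under Interventions, "each group is labelled with their respective intervention product (IP) number without disclosing the content in the softgel". Under Assignment of Interventions, "A set of numbers, from 1 to 60, is randomized using the randomization application for every block of 60 participants", followed by the parity rule: "All even numbers are treated with the same IP, while odd numbers are treated with another IP". The Analyses section confirms the result, "with 110 participants receiving each IP". The participant-specific code described under Recruitment labels laboratory results. No participant-level product code is described.

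**Code breaks.** Assignment of Interventions makes the PI responsible for breaking the blind of individual participants in an emergency, with decoding open to the PI and to designated sponsor personnel. Where the sponsor unblinds someone for expedited reporting, the identity stays with designated sponsor staff, and an effort is promised to keep other trial members blinded.

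**Triggers.** The same section says that "in case of any serious adverse event reported during the study period, the unmasking of the code is immediate". It later says that emergency unblinding is "only permitted in case of a suspected, unexpected serious adverse reaction or other important adverse event", and adds the condition that product identity must be needed to treat the participant.

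**Allocation.** Interventions: "Contract research assistants generated the random allocation sequence, enroll participants, and assign participants to the interventions". Assignment of Interventions: "Assignment of supplements to participants is by chance through the drawing of lots by contract research assistants", alongside the application-randomized list of 1 to 60.

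**The PI's other roles.** Under Recruitment the PI selects participants and may withdraw them at discretion. Under Monitoring the PI judges whether an adverse effect is related to the trial and whether the participant should leave it.

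**The concern.** An individual code break is useful only if it discloses one person's treatment. With two shared IP numbers, what is decoded is the meaning of an IP number, and that applies to everyone. The person named to perform the break is also the one whose judgments on selection, withdrawal and relatedness most need protection.

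The conflicting triggers matter because they govern how often this could happen: one makes unmasking automatic for any serious adverse event, the other makes it conditional.

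Concealment is a separate weakness. A sequence generated by the staff group that also consents, enrolls and assigns can be foreseen by whoever generated it. Before any break, a foreseen IP number does not give the treatment. It can still influence who is enrolled next if staff have formed a view, right or wrong, about which number is active.

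At stake are PI withdrawal decisions and the assessor-dependent outcomes, chiefly the cognitive tests, which are secondary endpoints. Analyzer, ELISA and HPLC results are much less exposed. Skin and arteriography measures are device readings and lie between the two.

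**Working it through.** **Step 1: the article's own balance claim.** The numbers 1 to 60 contain 30 even and 30 odd, so each full block is 30:30. The stated equality within blocks is reproduced.

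**Step 2: disclosure from one decoded participant.** Inputs: 220 participants, 110 per arm, k product codes per arm spread evenly.

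- If k = 1, the decoded code gives 110 arms and elimination gives the other 110.
- If k > 1, the decoded code gives 110/k arms. Of the 2k − 1 remaining codes, k belong to the opposite arm, so the best guess for anyone else is right with probability k/(2k − 1).

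| Codes per arm (k) | Arms certain after one break | Best guess for the others |
|---|---|---|
| 1 (as written) | 110 + 110 = 220 | 1 (certain) |
| 2 (assumed) | 110/2 = 55 | 2/3 = 0.667 |
| 5 (assumed) | 110/5 = 22 | 5/9 = 0.556 |
| 10 (assumed) | 110/10 = 11 | 10/19 = 0.526 |
| 110 (unique codes) | 1 | 110/219 = 0.502 |

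Only k = 1 follows from the article; the other rows are for comparison.

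**Step 3: who is affected.** The result applies to a person who both learns the decoded content and can see IP numbers. The PI learns the content by performing the break. Bottles carry the IP number and are returned at the 3- and 6-month visits. Under this scheme the IP number is also what must be looked up to unblind anyone. That the PI can see other participants' IP numbers is inferred. A break kept within the sponsor gives site staff nothing, because the sponsor labels the product and already knows what each number means.

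**Step 4: the two triggers side by side.** Take a serious adverse event that is expected, or for which product identity would not change treatment. The first statement unmasks at once. The second requires product identity to be needed for treatment, and so does not permit it. Both cannot be followed.

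**Step 5: the allocation accounts.** Drawing lots and working down a pre-randomized list are different procedures with different concealment properties. Generation, enrollment and assignment sit with one staff group. The article does not say who keeps the list, or whether the same individual generates and enrolls.

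**Step 6: how many a change can still reach.** Results reports 211 recruited and 167 completed as of April 2025. Not recorded as complete: 211 − 167 = 44. Still to recruit: 220 − 211 = 9. Together 53, before any replacements. The Abstract gives 209 recruited, which changes the split to 42 and 11 but not the total, since 220 − 167 = 53.

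**The case against.** **No break is reported.** Correct: the article still places unblinding after data collection. What is shown is a weakness in the scheme, not a loss of blinding.

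**The promise to keep others blinded can be kept.** For sponsor-level breaks this stands. The promise closes the paragraph on sponsor unblinding and expedited reporting, and two-code labeling can honor it there. It cannot protect the PI after a PI-level break.

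**A reader might infer that any serious adverse event unmasks the whole trial, and is nearly certain to occur.** With an assumed 6-month risk p per person, 1 − (1 − p)^220 is 0.668, 0.890 and 0.988 for p = 0.5%, 1% and 2%. These are chances of at least one serious adverse event at rates the article does not give. They would describe trial-wide unmasking only if the first trigger governed, the second were ignored and the result spread beyond the person decoding. The article supports none of these, so the figures do not measure this problem.

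**A reader might infer that enrolling staff hold the list and know each upcoming treatment.** The article says only that the assistants generated the sequence. Custody is not stated, and a foreseen IP number is not a foreseen treatment while its meaning stays with the sponsor. The lack of any stated separation of roles stands.

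**Most outcomes are instrument or laboratory measures.** This stands and limits the likely bias. Nor does the article say that decoded results pass to the staff who run the cognitive tests or arteriography.

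**Lots versus list may be loose wording in a condensed article.** Possibly; one corrected sentence would settle it.

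**Conclusion.** The concern holds in this form. As written, one PI-level code break determines the arm of all 220 participants for anyone who learns the result and sees IP numbers, so the individual break cannot preserve the PI's blinding to the rest. This follows from the parity rule and the group-level labels and needs no assumed event rate. It assumes that no participant-level product code exists beyond what the article describes, and that the PI can see IP numbers.

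The two unblinding statements contradict each other and must be reconciled; which clinical rule should apply is not judged here. Placing generation, enrollment and assignment in one staff group is a stated weakness in concealment, with list custody unknown. Actual bias cannot be sized from the article. It would fall mainly on PI withdrawal decisions and the secondary cognitive tests.

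**What to change.** 1. For participants still to be supplied, have the sponsor issue unique participant-level bottle codes, each with a single-participant code break. This protects new enrollees cleanly. For someone who already has one of the two IP numbers, a break would still reveal what that number means to anyone who knows it, so old numbers should be kept out of the PI's view.
2. Give the analyst scrambled arm labels in a data set without IP numbers. Plasma vitamin E is measured at every visit, so a comparison by IP number could itself suggest which product is active. Analysis of the first 120 participants is complete; the article does not say whether vitamin E was included.
3. Replace the two unblinding statements with one, the rule itself being left to those responsible for it.
4. For remaining allocations, have an existing person who neither enrolls nor belongs to the sponsor hold the list, and describe one allocation method. Sponsor custody would sit badly with the stated independence of trial conduct.
5. Record any code break to date and who learned the result. If any occurred at PI or site level, add a sensitivity analysis excluding later assessments; if none did, say so.

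Cost: relabeling of remaining stock, a short amendment and at most one extra analysis. Relabeling reaches at most 53 of the planned 220 (before replacements), fewer if some of the 44 have withdrawn or already hold their full supply. It cannot protect the 167 who have completed; for them the log of breaks and the sensitivity analysis are the only remedy.

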### Data Collection and Management

During the screening process, potential participants are assessed for eligibility to enter the study according to the inclusion and exclusion criteria. After an overnight fast, a 10-mL blood sample is taken from each volunteer. The screening tests consist of comprehensive evaluations, encompassing blood lipid profile, liver function tests, renal profile, full blood count, and fasting blood glucose measurements. Additionally, records of past supplementation and medical history are reviewed to obtain a holistic understanding of the individual’s health status. The results of blood tests are revealed to volunteers upon request. Volunteers who meet the inclusion criteria are selected for baseline sampling typically within a timeframe of 1 month to 2 months after the screening process.

Eligible participants are contacted to schedule appointments for data collection at baseline, 3 months, and 6 months. During each visit, a physician conducts a comprehensive medical evaluation, encompassing an assessment of medical history; documentation of any concurrent medications; measurements of participants’ weight, height, resting blood pressure, pulse rate, and temperature; and evaluation of vital signs. Subsequently, blood samples are drawn from each participant for immediate analysis of blood biochemistry, and additional samples are preserved for future analysis of oxidative stress markers, inflammatory markers, vitamin E, and appetite regulation marker levels. Furthermore, on the same day as the visit, assessments are performed for arterial stiffness, body fat composition, skin health, bone mineral density, and cognitive function.

Participant records and data for analyses are kept in separate folders according to the protocol and transferred into the CRF of each participant by the contract research assistants. The result for each assessment is monitored by specific investigators with expertise in the field, to facilitate comprehensive monitoring of the data.

A contractual disclosure agreement signed by the sponsors and investigators outlines the sponsor’s access rights to the trial data set and source data. Both the investigators and sponsor should collaborate and jointly author publications reporting the trial’s results to ensure an accurate representation of the results and drawing of appropriate conclusions, thereby preserving the integrity of the findings. All data are reported in a collective manner with no reference to any participants in the trial to ensure that the identities of participants remain confidential.

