### Sample Size

Sample size estimation was based on a comparison of mean low-density lipoprotein levels, referencing a previous case-control study on biomarkers for premature coronary artery disease by Shukor et al [99]. The sample size was calculated using a power and sample size program. The effect size was calculated based on a mean value of 3.11 (SD 0.81) for group one and a mean value of 2.66 (SD 1.25) for group two.

The total number of required participants calculated per group of the experimental design was 93 when dichotomous outcomes were presumed with a Type I error probability, α of .05, and power of 0.8. To maintain the power, a 20% dropout rate was factored in. Consequently, 110 participants are required to be enrolled in each group (placebo and supplementation). Therefore, a total of 220 participants are required to perform this clinical study.

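### Blood biochemistry is measured twice before supplementation, but the described ANOVA treats month 0 as a level of time and gives the screening value no role; adjusting for both would sharpen these comparisons without extra sampling

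*Protocol article*

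**What the plan says.** Data Collection and Management describes the screening draw, taken after an overnight fast: "The screening tests consist of comprehensive evaluations, encompassing blood lipid profile, liver function tests, renal profile, full blood count, and fasting blood glucose measurements". Volunteers who qualify are "selected for baseline sampling typically within a timeframe of 1 month to 2 months after the screening process". Outcomes and Table 1 then place blood biochemistry at months 0, 3 and 6, with the same type of analyzer as at screening. Every enrolled participant should therefore have two pre-supplementation values for this panel.

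Blood biochemistry is listed among the primary end points, and LDL is the variable behind the sample size: "Sample size estimation was based on a comparison of mean low-density lipoprotein levels".

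The Analyses section names a mixed-design ANOVA with measurements "at baseline, 3 months, and 6 months among the groups". Month 0 is thus one of the repeated outcomes. Linear mixed-effects models are planned for missing data. The only covariate named in the article is the compliance percentage (Monitoring). The one stated use of the screening value is to decide eligibility.

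**The concern.** A single blood value carries day-to-day variation. In a mixed-design ANOVA with month 0 as a time level, the treatment effect is read from the group-by-time term. At month 6 that amounts to comparing changes from one noisy baseline, and the noise in that baseline enters the variance in full. Using pre-treatment values as covariates avoids this, and a second pre-treatment value predicts follow-up better than one. At stake is the width of the interval for LDL and the rest of the panel. Validity is not in question, and the data are already held.

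**Working it through.** **The plan's own figure.** The inputs in Sample Size are a "mean value of 3.11 (SD 0.81) for group one and a mean value of 2.66 (SD 1.25) for group two", with "Type I error probability, α of .05, and power of 0.8". The difference is 0.45 and the mean variance is (0.81² + 1.25²)/2 = 1.109 (SD 1.053). Taking α as two-sided, n = 2 × (1.960 + 0.842)² × 1.109 / 0.45² ≈ 86 per group, or 87 with the t test. The protocol states 93, so the figure is not reproduced; that is a separate matter. What counts here is that the calculation uses raw between-person SDs and takes no credit for any baseline value.

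**Set-up.** Let S be the screening value, B the month-0 value and Y the month-6 value. Each has unit variance, and every pair has the same correlation r. The documents give no r, so it is an assumption, shown over a range. Per-participant variance of the treatment contrast:

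- change from month 0 (the planned type of contrast): 2(1 − r)
- adjusted for B only: 1 − r²
- adjusted for B and S: 1 − 2r²/(1 + r)

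For r = 0.5 these are 2 × 0.5 = 1.00; 1 − 0.25 = 0.750; 1 − 0.50/1.5 = 0.667.

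| r | Change | B only | B and S | B and S vs change | B only vs change | B and S vs B only |
|---|---|---|---|---|---|---|
| 0.3 | 1.40 | 0.910 | 0.862 | −38% | −35% | −5.3% |
| 0.5 | 1.00 | 0.750 | 0.667 | −33% | −25% | −11.1% |
| 0.6 | 0.80 | 0.640 | 0.550 | −31% | −20% | −14.1% |
| 0.7 | 0.60 | 0.510 | 0.424 | −29% | −15% | −17.0% |
| 0.8 | 0.40 | 0.360 | 0.289 | −28% | −10% | −19.8% |

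**Adding S to the planned test and changing nothing else.** Cov(S, Y − B) = r − r = 0, so under equal correlations the gain is nil. The benefit needs the change of model.

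**Selection on the screening value.** The Discussion says about 60% of volunteers qualified, with high LDL among the main reasons for exclusion. Screening values were simulated with an upper cut-off that keeps 60% or 80%. The gain from S beyond B was then 5.7% or 7.4% at r = 0.5, 8.1% or 10.1% at 0.6, 10.7% or 13.0% at 0.7, and 14.2% or 16.4% at 0.8. Under the same normal model, Y − B is unrelated to S, and the residual variance given both values does not change. So the total against the change contrast stays at 28–33%; only the share due to S shrinks.

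**Weaker correlation over the longer gap.** Screening lies 1–2 months further from month 6. Set the S–Y correlation 0.05 below the other two. The gain from S beyond B is then 7.1% (others 0.5), 9.8% (0.7) or 9.3% (0.8). Combined with the gain from B alone, the total against the change contrast is:

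- others 0.5: 1 − 0.75 × 0.929 = 30%
- others 0.7: 1 − 0.85 × 0.902 = 23%
- others 0.8: 1 − 0.90 × 0.907 = 18%

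Steeper decay leaves S adding less. The gain is 4.8% for correlations S–B 0.6, B–Y 0.6, S–Y 0.5; 2.8% for 0.8, 0.8, 0.7; and 0.9% for 0.8, 0.7, 0.6.

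**The case against.** The strongest reply is that nothing in the plan is wrong. A screening covariate is optional, and an analysis plan that is not shown could already include one. The Analyses section does not exclude it. Its account of the mixed models refers to observed predictors without listing them, and the parenthesis after blood biochemistry in the ANOVA sentence names inflammation and oxidative stress, not lipids. That the screening value goes unused is therefore an inference from the listed time points and the single named covariate. This stands, and it limits the point to a recommendation.

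The two draws may also not be interchangeable. Outcomes specifies the 8–10 AM draw and the 8- to 10-hour fast for baseline, 3 and 6 months, whereas screening is described only as following an overnight fast. This stands too. It is a reason to let the model weight the two values separately.

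Four stronger readings are tempting, and the documents do not support them:

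- *The comparison is biased.* It is not. Selection on a value taken before supplementation affects both randomised groups alike.
- *The stated power is eroded.* It is not. The sample size never relied on a baseline value.
- *Ignoring screening costs 11–20% outright.* That range holds only for r of 0.5–0.8 and compares two baseline-adjusted models, neither of which is planned.
- *Averaging screening into baseline is simpler and gains more.* For a change contrast at one follow-up visit, averaging would cut variance by 25% whatever r is. But eligibility is judged on the screening value, so regression to the mean would distort the description of within-group change.

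**Conclusion.** The point holds as a modest, optional improvement. With equal correlations of 0.5–0.8, adjusting for both pre-supplementation values lowers the variance of the month-6 contrast by about 28–33% against the planned change-type contrast. Standard errors are then about 15–18% smaller (√0.722 = 0.85, √0.667 = 0.82).

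At the lower correlations much of this comes from using month 0 as a covariate at all. The screening value itself adds about 11–20%, or roughly 6–16% once selection on LDL or slight decay is allowed for. It adds about 5% at r = 0.3, and less if correlation fades quickly with time. Slight decay also lowers the total, to about 18–30%.

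All of these figures rest on correlations that the protocol does not give. The gain is confined to the blood biochemistry domain. Oxidative stress, TNF-α and IL-6, appetite hormones, skin and arterial stiffness have no screening value.

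**What to change.** For lipids, liver, renal, blood count and fasting glucose, replace the group-by-time test with a baseline-adjusted model. This can be ANCOVA at month 6, or a mixed model with months 3 and 6 as outcomes. Enter the month-0 and screening values as two separate covariates. Month 0 must then not also be an outcome level. Keep month 0 as the reference when describing change.

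State this in writing before the product codes are revealed. Results reports that data for the first 120 participants have already been analysed, so the choice should be dated and recorded as made without knowledge of treatment.

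The cost is a different model form for these endpoints and two covariate degrees of freedom per outcome. No new sampling is needed.
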